##### Secondary outcomes

*Consumption frequencies of main food groups and water/hot drinks* are assessed using data from two 24-hour diet recalls and one FFQ.

*Physical fitness* is assessed using the French version of the Senior Fitness Test battery [55]. Besides the 30s Chair Stand Test which indicates lower-body strength (see primary outcomes), it also includes: (i) the Arm Curl Test (upper-body strength); (ii) the 2-minute Step Test (aerobic endurance); (iii) the Chair Sit and Reach Test (lower-body flexibility); (iv) the Back Scratch Test (upper-body flexibility); and (v) the Get Up and Go Test (dynamic balance). Additionally, the Open-Eye Stand on Dominant Foot Test assesses static balance. According to the range of scores [56], there are four levels for each physical parameter: low, below average, to be maintained, and good.

*Overall level of physical activity* is assessed by (i) the number of steps recorded with a pedometer (Yamax Power-Walker EX_™_-210) during 1 week and reported by the participant on a weekly notebook provided by the APA professional; (ii) the *Questionnaire d’activité physique pour personnes âgées* (QAPPA) self-reported physical activity questionnaire for the elderly [57]. This 7-day recall questionnaire includes 4 items on moderate and intense physical activity. Scores are calculated using the number of minutes of each type of activity reported in metabolic equivalent per week and individuals are then classified into three activity levels (low, moderate, or high).

*Quality of life* is measured by the SF-12 V1 Health Survey questionnaire [58] which includes 12 questions corresponding to the following eight domains: 1) Limitations in physical activities because of health problems; 2) Limitations in social activities because of physical or emotional problems; 3) Limitations in usual role activities because of physical health problems; 4) Bodily pain; 5) General mental health; 6) Limitations in usual role activities because of emotional problems; 7) Vitality; and 8) General health perceptions.

*Feelings of loneliness* are assessed using one item of the environmental dimension of the FRAGIRE tool for assessing an older person’s risk for frailty [59]: “Do you feel lonely or abandoned?” (*Not at all*, *A little*, *Quite a bit, A lot).*

#### Process evaluation

Intervention fidelity, dose, and reach are assessed using data obtained from attendance lists, information sheets completed by local organizations, information sheets completed by dieticians and APA professionals after each session, and self-administered questionnaires that are completed by participants during T1 and T2 (e.g., self-reported exercises from everyday tasks; participation in post-session activities between participants, see Additional file 5) [60]. To ensure fidelity, and to make sure that the program is transferable, we will also document how the actors who are involved in the program interact [61], in comparison with planned interactions.

To explore how the intervention might modify outcomes, we will analyze data from the self-administered questionnaires to be completed by participants at T0, T1 and T2, especially from the questions that assess the major constructs of the Theory of Planned Behavior [48] (beliefs, attitudes, and intention, see Additional file 5). In the Theory of Planned Behavior questionnaires, the behavior of interest must be clearly defined in terms of target, action, context, and time elements. We measured the beliefs, attitudes, and intention of physical activity (“daily physical activity in the next 3 months”) [62], but found that the questions were not applicable to dietary diversity. We also conduct semi-structured individual interviews with approximately 20 participants from the intervention group, who accepted to be contacted again, to gain a better understanding of how/why participation in ALAPAGE workshops improves (or does not improve) eating behaviors, physical activity, and quality of life, as facilitators and barriers to behavior changes that participants encountered.

#### Cost-effectiveness evaluation

All unit costs (e.g., hourly cost for dieticians, APA professionals) and quantities required (e.g., total number of working hours) were listed and collected in advance from the local organizations who are responsible for the intervention and control workshops. These costs will then be compared to the effectiveness of the intervention (outcomes related to eating behaviors, physical activity, and Quality Adjusted Life Years, QALYs [63]) using the cost-effectiveness ratio (i.e., incremental costs divided by the incremental health benefits) [64].

#### Sample characterization

Sociodemographic data (e.g., age, sex, educational level, perceived financial situation, frequency of participation in social activities) as antecedents towards physical activity and history of falls are also collected through self-questionnaires (see Additional file 6).

### Data collection procedure

Data collection is performed on the premises of local organizations under the supervision of a dietician and/or an APA professional, except for: one 24-hour recall performed at home during week 5 for the control group and during week 18 for both groups; and the number of steps during 1 week recorded at home three times for each group (Table 2).

Face-to-face interviews with participants are performed by researchers, who have significant qualitative research experience, in the month following T2 at the local organization or at home depending on the participants’ preference.

All study participants will be financially compensated (the intervention group will receive a 15 € voucher; the control group will receive two 15 € vouchers, the second voucher compensating for the additional participation in the measurement visit).

Expected and non-expected serious adverse events and other unintended effects of the intervention (i.e., those that require hospitalization, result in a significant or long-lasting disease/disability, or death) are collected and immediately reported to the research team by the sessions’ dieticians and APA professionals.

Prior to the commencement of the study, dieticians and APA professionals participate in training sessions that are led by research team members (including by one person who is certified in Good Clinical Practices [GCP]) and includes (i) a two-hour video conference that presents the study and its data circuit; (ii) a half-day session on research issues (e.g., clinical practices, information, consent, notification of adverse events); and a further one and a half day session on the study’s content and visits (e.g., program, objectives, tools).

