## Methods

### Study design and setting

The ALAPAGE study is a pragmatic cluster randomized controlled trial (cRCT) [43] with two parallel arms using a 2:1 ratio. It is performed among older people who live at home in southeastern France (intervention period: January 2022–October 2023). A cluster consists of approximately 10 people participating in a “workshop”, which is defined as a collective intervention that is conducted on the premises of local organizations (e.g., municipalities, social/community centers). A total of 45 workshops are randomized into two groups: (i) the intervention group (corresponding to 30 workshops), who benefits from the ALAPAGE program; and (ii) the control group (corresponding to 15 workshops), who will only benefit from the ALAPAGE program after the completion of the study (waiting-list control group).

The complete study duration for participants is four and a half months (19 weeks; see Fig. 1 for an overview of the study). Participants in the control group have measurement visits, but no intervention visits before benefiting from the ALAPAGE program.

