Each intervention workshop includes (i) a 7-week intervention period with weekly collective sessions supported by a dietician and/or a qualified APA professional (one introductory session, 4 sessions on diet, and 2 sessions on physical activity, each 2.5 hours in duration); followed by (ii) a 12-week intervention period that consists of a post-sessional program of activities among participants without the supervision of a professional (see Table 1 for more details). As part of this pragmatic trial, professionals (e.g., dieticians, APA professionals and staff from local organizations) have some flexibility in the implementation of the ALAPAGE program in order to take into account for “real-life” constraints (e.g., they can opt for a two-week interval between sessions instead of a one-week interval) [43]. Compared to existing workshops, the ALAPAGE program newly addresses the following themes: dietary diversity, nutritional profiles, budget (healthy eating on a budget), sustainable diet and, regarding physical activity, balance, flexibility, strength and aerobic exercises incorporated into everyday tasks [37], and a 10-minute routine exercise (see Table 1 for more details). The ALAPAGE program uses innovative tools developed as part of the participation process and involved dieticians, APA professionals, and elderly people.

**Table 1 Tab1:** Overview of the ALAPAGE program^a^

Content of the ALAPAGE program	Supervisor(s)

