**Post-session program of activities between participants (e.g., walking).**	

*APA* adapted physical activity, *S0-S6* diet and physical activity sessions of the ALAPAGE program

^a^Each session lasted 2 h30

^b^A weekly notebook for physical activity self-reporting is also provided to participants in each following session from S1 to S5

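### Only serious harms are collected, through session staff who have no scheduled contact in weeks 8–18 and see the arms unequally before that; matched questionnaire items at weeks 7 and 19 would be a cheap improvement

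*Protocol article*

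**What the plan says.** Data collection procedure gives the reporting rule for harms in one sentence. Serious adverse events, expected or not, and other unintended effects of the intervention "are collected and immediately reported to the research team by the" sessions' dieticians and APA professionals. The threshold follows directly after the words on unintended effects, "i.e., those that require hospitalization, result in a significant or long-lasting disease/disability, or death", so it reads as governing those effects as well as the serious adverse events.

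The schedule has two phases. Intervention group describes "a 7-week intervention period with weekly collective sessions supported by a dietician and/or a qualified APA professional", followed by "a 12-week intervention period that consists of a post-sessional program of activities among participants without the supervision of a professional". Table 1 gives the content of the second phase as "Post-session program of activities between participants (e.g., walking". Controls attend measurement visits only.

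Falls appear under Sample characterization, where "history of falls are also collected through self-questionnaires", and under Data analysis, where history of falls is a planned moderator. Table 2 lists no outcome that counts falls or injuries during follow-up.

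**The concern.** The program trains balance, strength, flexibility and aerobic exercise built into everyday tasks, plus a 10-minute routine, in people aged 60 and over. The harms one would most want to know about are falls and strains, and most of these would not reach the stated threshold. The reporting route is also tied to staff whose scheduled contact stops at week 7 for 12 weeks and who, until then, meet one arm more often than the other.

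Two things are at stake. The trial could end without usable information on non-serious falls and injuries, although the Discussion looks to wider reach of the program through its operational partners. And if harms are described by arm, part of any difference could reflect how often staff saw people rather than what happened to them.

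**Working it through.** **Inputs.** Contact weeks come from Table 2, counting only contacts with a dietician or APA professional (the home entries are not such contacts). Sample sizes and dropout come from Sample size calculation.

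- Intervention: S0–S6 in weeks 1, 2, 3, 4, 5, 6, 7; V3 in week 19.
- Control: V0, V1, V2, V3 in weeks 1, 2, 7, 19.
- Enrolment 300 and 150; dropout between T0 and T2 assumed at 30%.

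**The plan's own figure.** 7 weeks of sessions + 12 weeks post-session = 19 weeks. This agrees with Study design and setting: "The complete study duration for participants is four and a half months (19 weeks; see Fig. 1 for an overview of the study".

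**Contacts and gaps.** If events are spread evenly over a period with gaps g between contacts, the mean wait to the next contact is Σ(g²/2) / Σg.

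| | Intervention | Control |
|---|---|---|
| Contacts, weeks 1–7 | 7 | 3 |
| Contacts, weeks 8–19 | 1 | 1 |
| Total | 8 | 4 |
| Gaps, weeks 1–7 | six of 1 week | 1 and 5 weeks |
| Mean wait, weeks 1–7 | (6 × 0.5)/6 = 0.5 weeks | (0.5 + 12.5)/6 = 2.2 weeks |
| Gap, week 7 to week 19 | 12 weeks | 12 weeks |

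The imbalance is therefore confined to weeks 1–7. After week 7 the two arms are observed equally, and equally little.

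**Period without scheduled contact.** Weeks 8 to 18 inclusive are 11 weeks, and 11/19 = 58% of follow-up. An event just after week 7 could wait up to about 12 weeks for the next scheduled meeting with a named reporter, unless someone reports it unprompted.

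**Dropout.** 0.30 × 300 = 90 and 0.30 × 150 = 45 participants might not be seen at V3, at the planning assumption.

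**Threshold against content.** Set beside the exercise content in Intervention group and Table 1, the stated threshold leaves out a fall or musculoskeletal injury without hospitalisation or lasting consequence, in either arm and at any time. Fall history at entry does not fill that gap, since it describes the sample and not follow-up.

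**Control arm.** The wording refers to effects of the intervention and to session staff. It does not say outright that the same collection applies at control visits.

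**The case against.** The strongest reply is that this is a condensed article. A full protocol (version 3.0) exists and is not shown, professionals receive training that covers notification of adverse events, and the questionnaires are in additional files that are not shown either. A participant reporting route or a harms item may be described there. This stands as a limit on the point. It does not remove it, because the article does state who reports and above what threshold.

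Four stronger readings are tempting, and the text does not support them.

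- *That immediate reporting is impossible in weeks 8–18.* The word can mean without delay once the professional knows of the event, and on that reading nothing contradicts the schedule.
- *That no harms can be captured in the last 12 weeks.* Unsolicited reports from participants or host organizations are not ruled out. What is missing from the description is a scheduled, solicited route.
- *That the trial will find more harms in the intervention arm.* More contact gives more opportunity to notice events, but without event rates neither the presence nor the size of a bias can be shown. Events as serious as those collected are less likely to be lost over the controls' 5-week early gap.
- *That a planned comparison of harms is invalid.* Harms are not among the objectives or the Table 2 outcomes, and Data analysis plans no test of them. The concern applies to any description of harms by arm.

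It is also fair to say that collecting only serious events in a community prevention program is a judgement of proportionality, and that the only post-session activity named is walking. But the exercises taught are meant for daily life, and self-reported exercise in daily activities is asked about again at V3, so continued home exercise is expected.

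**Conclusion.** The point holds as a cheap improvement to harms collection. It does not threaten the primary analyses. Followed as stated:

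- non-serious falls and injuries are not recorded in either arm;
- serious events in weeks 8–18 (11 of 19 weeks) rely on unsolicited reports;
- any description of harms by arm rests on 7 against 3 contacts in the session phase, although contact is equal afterwards.

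This assumes the nominal weekly schedule in Table 2 (Intervention group allows two-week intervals between sessions) and no further reporting route in the full protocol. The size of any bias cannot be stated.

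**What to change.** Add one short, identical item set to the self-questionnaires that both arms already complete at T1 and T2: any fall, injury or hospitalisation since the previous questionnaire, with its date.

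- **Timing.** Give the items at the shared week-7 (S6/V2) and week-19 (V3) contacts, where Table 2 already places the QAPPA questionnaire in both arms. Do not attach them to the SF-12, which falls in week 6 for the intervention arm and week 7 for controls, or recall windows will differ. Dates also help where a workshop has used longer intervals between sessions.
- **Checking.** Have the professional read the answers at the visit. Under Data management, forms stay locked at the local organization until the study is complete, so unread answers would alert nobody.
- **Wording.** In Data collection procedure, extend other unintended effects to non-serious falls and injuries, and state that the reporting rule applies to both arms and to weeks 8–18.
- **Reporting.** Describe harms by arm from the solicited items only.

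The cost is a few questionnaire lines, slightly more participant burden and some data entry, with no extra visit. The limits are that self-report is unblinded and that participants who drop out before V3 are still missed.

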### Sample size calculation

Sample size calculations are based on the (i) research team’s preliminary results on dietary diversity and the development of the DAS [53], and the research team’s consensus on the intervention’s effect size of + 1 standard deviation between T0 and T2; (ii) impact on older people’s lower-limb muscle strength from a previous intervention that showed similarities with the exercises proposed in the ALAPAGE program [65]. We performed power calculations using simulations (10,000 samples per simulation, see Additional file 7 for more details) assuming α = 0.05, similar characteristics of participants in both groups, a 30% dropout rate between T0 and T2, and an intra-cluster correlation of 0.03 [22, 66]. Based on these simulations, we intend to enroll 300 participants in the intervention group (i.e., 30 workshops with 10 participants in each) and 150 participants in the control group (15 workshops with 10 participants in each); this provides a 95% power for both primary outcomes.

### Data management

The participants are each given a unique identification code (without any personal information that could allow for their identification). During the study period, all of the collected data is stored in a locked cabinet at the local organizations, according to a procedure compliant with GCP guidelines. When the study is complete, the collected data will be securely transmitted to the research team’s logistic department, who will create the databases. The collected data will be stored according to standards for archiving research materials.

Leaders of the research team who are involved in the ALAPAGE study and who have signed a consortium agreement will have access to the final study dataset.

### Data analysis

All statistical analyses will be performed using SAS 9.4 (SAS Institute Inc., Cary, NC, USA). A α of 0.05 will be used to determine statistical significance.

First, descriptive statistics (mean ± standard deviation, median, and frequency distribution) will be carried out to describe baseline characteristics (sociodemographic, life conditions, primary and secondary outcomes) of participants in both groups. To compare the baseline characteristics (age, gender, life conditions) between the two groups, a one-way ANOVA or a Kruskal-Wallis test will be used for continuous variables and a Chi-square or a Fisher’s exact test will be used for categorical variables.

As part of the effectiveness evaluation, linear or logistic (depending on the nature of the dependent variable) mixed models will be carried out to study the impact of the intervention on primary and secondary outcomes, while taking into account the repeated nature of the data and the intra-cluster correlation. Time, group and their interaction will be defined as fixed factors (see Additional file 7 for more details). If imbalances occur between the groups, the baseline values will be added as covariates in the models. Missing data will be inspected, and, if appropriate, will be handled using multiple imputation.

As part of the process evaluation, we plan to perform mediation analyses to verify whether beliefs, attitudes, and intention are pathways by which the intervention impacts physical activity. Furthermore, we plan to perform moderating analyses to test whether the effect of the intervention varies according to some characteristics (in particular, type of recruitment, antecedents of physical activity or history of falls, and baseline dietary diversity).

As part of the process evaluation, qualitative data from participant interviews of the intervention group will be transcribed and analyzed using a data-driven inductive approach to explore how the intervention may have resulted in behavioral changes.

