We must also acknowledge some limitations. First, the recruitment of participants will take place after the randomization of workshops. This may lead to recruitment bias and a discrepancy in the characteristics of the participants in both the intervention and the control groups [68]. As part of this pragmatic cRCT, our operational partners did not find it feasible to recruit participants before the cluster randomization or by means of a blinded and independent person. To limit recruitment bias (e.g., participants in the intervention group are more interested in diet and physical activity issues and are thus more likely to change their behaviors than those in the control group), we will use a waiting-list control group design. Consequently, all participants are interested in participating in workshops on diet and physical activity. Second, due to feasibility constraints, the times points differ slightly between the intervention and control groups for some of the outcomes. However, we have done our best to limit these differences and to reconcile methodology requirements and practical feasibility. We hypothesize that this will have a limited impact on our results. Lastly, we cannot exclude differing attrition rates between the intervention and control groups that may lead to biased estimates of the intervention’s effects. In this instance, we plan to use appropriate econometric techniques (e.g., a Heckman sample selection correction model [69]) to correct for attrition bias [70].

The results of this study should help to implement public health interventions that are effective at improving dietary diversity, physical activity and fitness, and social outcomes among older people who live at home. They will contribute to the improvement of healthy aging while limiting social inequalities. The ALAPAGE program has been developed and will be evaluated in close relationship with major operational partners of healthy aging in France, thus providing a unique opportunity to expand its reach.

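### Baseline comparisons between arms use tests that ignore the workshop clustering, so a nominal 5% test rejects in about 8% of cases at the plan's own ICC of 0.03

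*Protocol article*

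**What the plan says.** The unit of randomisation is clear. Under Study design and setting the protocol article states: "A total of 45 workshops are randomized into two groups", in "two parallel arms using a 2:1 ratio". The Sample size calculation section plans "300 participants in the intervention group (i.e., 30 workshops with 10 participants in each"), with 15 workshops of 10 as controls, and assumes "an intra-cluster correlation of 0.03".

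The Data analysis section sets the general significance level: "A α of 0.05 will be used to determine statistical significance". It then promises descriptive statistics for both groups and names the baseline tests. The purpose is given as "To compare the baseline characteristics (age, gender, life conditions) between the two groups", and the method is that "a one-way ANOVA or a Kruskal-Wallis test will be used for continuous variables and a Chi-square or a Fisher’s exact test will be used for" those that are categorical. No clustering adjustment is attached to these tests.

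The next paragraph of that section uses mixed models for the outcomes and says that they account for intra-cluster correlation. It also says that baseline values will be added as covariates if the groups are imbalanced, without defining imbalance.

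The Discussion lists recruitment after randomisation as its first limitation: "This may lead to recruitment bias and a discrepancy in the characteristics of the participants in both the intervention and the control groups".

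**The concern.** One-way ANOVA, Kruskal-Wallis, Chi-square and Fisher's exact test take their null distributions from independent participants. Here people enter in groups of about 10, through the usual channels of a particular local organization or by active recruitment in the municipality that hosts the workshop. Age and life conditions can therefore plausibly differ between workshops even when recruitment is even-handed across arms. A participant-level test counts that variation as evidence of an arm difference.

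In an individually randomised trial, baseline p-values answer little, because any difference is due to chance. In this trial they have a real question to answer: did knowledge of the allocation change who was recruited? A test that rejects too often under even-handed recruitment answers it badly. What is at stake is the reading of the baseline table and, possibly, the choice of covariates.

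**Working it through.** **Inputs from the protocol article.** 30 and 15 workshops of 10 participants (Sample size calculation); significance level 0.05 (Data analysis; sidedness is not stated, two-sided is used here); ICC 0.03 (Sample size calculation, given for power only). The 30% dropout does not apply at baseline.

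**Assumed input.** The document gives no ICC for age, gender or life conditions. The values 0.05, 0.10 and 0.20 are shown as a range.

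**Formula.** With equal clusters of size m in both arms, the variance of the difference in arm means is multiplied by the design effect DE = 1 + (m − 1) × ICC = 1 + 9 × ICC. A participant-level test omits this factor. Its true size at nominal 5% is therefore 2 × (1 − Φ(1.96/√DE)).

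**Starting point.** The only error rate that the plan states is the nominal 5%. At ICC 0 the formula gives DE = 1 and 5.0%, and simulation gives 5.1% for ANOVA. The nominal level is thus reproduced when there is no clustering.

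**At the plan's ICC.** DE = 1 + 9 × 0.03 = 1.27; 1.96/√1.27 = 1.74; size = 8.2%.

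**Range, with a simulation check.** The simulation used 30 against 15 clusters of 10 with no arm difference: 20,000 runs for ANOVA, Chi-square and the cluster-level t-test, and 4,000 for Kruskal-Wallis. Chi-square is shown at a prevalence of 0.7.

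| ICC | DE | Formula | ANOVA | Kruskal-Wallis | Chi-square |
|---|---|---|---|---|---|
| 0.03 (document) | 1.27 | 8.2% | 8.0% | 8.0% | 8.4% |
| 0.05 (assumed) | 1.45 | 10.4% | 10.4% | 10.5% | 10.6% |
| 0.10 (assumed) | 1.90 | 15.5% | 15.5% | 16.0% | 15.9% |
| 0.20 (assumed) | 2.80 | 24.2% | 24.5% | 24.2% | 24.2% |

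Fisher's exact test was not simulated.

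**Comparator.** A t-test on the 45 workshop means rejects in 4.9% to 5.2% of simulated trials at every ICC from 0 to 0.20.

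**Not modelled.** Unequal workshop sizes, the four time-based randomisation blocks, and correlation between workshops with the same host. The article selects 25 organizations for 45 workshops, an average of 45/25 = 1.8 each, so some must host more than one. The effect of this on the error rate is not quantified.

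**The case against.** The best defence is that little depends on these tests. They sit in a descriptive step, and no effect estimate or confidence interval rests directly on them. The primary and secondary outcomes go into mixed models that allow for clustering. This stands. A reader might infer that the effectiveness results are compromised, and the document does not support that.

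A reader might also infer that a significant baseline test decides which covariates enter the outcome models. The article does not say so. The tests are listed for age, gender and life conditions, while the adjustment sentence speaks of baseline values, which may mean baseline outcome values. The tests might influence that decision, since no other criterion is given, but the link is not stated.

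Nor are these tests the only view of balance. The same section commits to means, standard deviations, medians and frequencies for both groups, and the Discussion offers the waiting-list design as a safeguard against recruitment bias.

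On size, the only documented ICC gives about 8% against 5%; the higher rates depend on assumed ICCs. A reader might go further and compound the rates over many characteristics. That would need a number of variables and an independence between them that the document does not supply.

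Finally, if workshops differ by chance, the enrolled arms really do differ, and for covariate adjustment the realised difference is what counts. That is fair, but it is an argument for looking at the size of differences. It does not make a participant-level p-value valid as a test of systematic selection, which is the question that recruitment after randomisation raises.

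**Conclusion.** The concern holds as a minor point. The plan names tests that do not match its unit of randomisation, in the same section that allows for clustering when it models outcomes. This is a stated choice and not a detail left to another document.

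The true size is about 8% at ICC 0.03, on the assumption that the power-calculation value also applies to baseline characteristics. It is about 10% to 24% if their ICCs lie between 0.05 and 0.20, which is a range assumed here. All rates are per variable and suppose equal workshops of 10, independent workshops and no systematic arm difference. Since recruitment follows randomisation, a flagged difference in the real data could also be genuine selection; the planned p-values are too small to tell the two apart.

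**What to change.** In the Data analysis section, replace the participant-level tests with a comparison that respects the workshop: for each baseline characteristic, a linear or logistic mixed model with group as fixed effect and workshop as random effect, or a comparison of workshop means. Report each arm difference with its cluster-adjusted 95% interval next to the descriptive statistics already planned, and judge possible recruitment bias from its size and interval. Because some organizations host more than one workshop, check whether the conclusions change when an organization-level effect is added.

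The cost is about one sentence in the plan and a few lines of SAS code, with no new data; mixed models are already planned. The drawback is wider intervals, so a small true imbalance will less often be labelled significant.
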